#### **11.3.6. Analyses of Other Parameters**

The duration of treatment and MRU data will be summarized descriptively.

Subgroup analysis (by geographical region or by country) of resistance status will be summarized descriptively.

### **11.4. Safety Analyses**

All safety analyses will be performed on the safety population.

All safety parameters will be listed in individual subject listings, sorted by randomized trial treatment group, center, and subject number.

**Adverse Events**

The original terms used in the CRFs by investigators to identify adverse events will be coded using the Medical Dictionary for Regulatory Activities (MedDRA). The percentage of subjects with specific treatment-emergent adverse events will be summarized for each treatment group. Adverse events will be summarized in frequency tables by severity and relationship to study drug.

Special attention will be given to those subjects who have discontinued treatment due to an adverse event or who experienced a severe or a serious adverse event.

**Clinical Laboratory Tests**

Laboratory data will be summarized by the type of laboratory test. Normal reference ranges and markedly abnormal results (specified in the Statistical Analysis Plan) will be used in the summary of laboratory data. Descriptive statistics will be calculated for each laboratory analyte at baseline and at each scheduled time point. Changes from baseline results will be presented in pre- versus posttreatment cross tabulations (with classes for below, within, and above normal ranges). A listing of subjects with any laboratory results outside the reference ranges will also be provided.

**Cardiovascular Safety**

ECG data will be summarized using descriptive statistics.

**Vital Signs and Physical Examination**

Descriptive statistics will be provided to evaluate the changes at each scheduled time point.

**12. ADVERSE EVENT REPORTING**

Timely, accurate, and complete reporting and analysis of safety information from clinical studies are crucial for the protection of subjects, investigators, and the sponsor, and are mandated by regulatory agencies worldwide. The sponsor has established Standard Operating Procedures in conformity with regulatory requirements worldwide to ensure appropriate reporting of safety information; all clinical studies conducted by the sponsor or its affiliates will be conducted in accordance with those procedures.

## 12.1. Definitions

### 12.1.1. Adverse Event Definitions and Classifications

- **Adverse Event**

An adverse event is any untoward medical occurrence in a clinical study subject administered a pharmaceutical product. An adverse event does not necessarily have a causal relationship with the treatment. An adverse event can therefore be any unfavorable and unintended sign (including an abnormal finding), symptom, or disease temporally associated with the use of a medicinal (investigational) product, whether or not related to the medicinal (investigational) product. (Definition per International Conference on Harmonisation [ICH])

This includes any occurrence that is new in onset or aggravated in severity or frequency from the baseline condition, or abnormal results of diagnostic procedures, including laboratory test abnormalities.

Note: The sponsor collects adverse events starting with the signing of the informed consent.

- **Serious Adverse Event**

A serious adverse event as defined by ICH is any untoward medical occurrence that at any dose meets any of the following conditions:

- results in death
- is life-threatening  
(The subject was at risk of death at the time of the event. It does not refer to an event that hypothetically might have caused death if it were more severe.)
- requires inpatient hospitalization or prolongation of existing hospitalization
- results in persistent or significant disability/incapacity, or
- is a congenital anomaly/birth defect

Note: Medical and scientific judgment should be exercised in deciding whether expedited reporting is also appropriate in situations other than those listed above. For example, important medical events may not be immediately life threatening or result in death or hospitalization, but may jeopardize the subject or may require intervention to prevent one of the outcomes listed in the definition above. Any adverse event is considered a serious adverse event if it is associated with clinical signs or symptoms judged by the investigator to have a significant clinical impact.

- **Unlisted (Unexpected) Adverse Event**

An unlisted adverse event, the nature or severity of which is not consistent with the applicable product information. For an investigational product, the expectedness of an adverse event will be determined by

whether or not it is listed in the Investigator's Brochure. For a comparator product with a marketing authorization, the expectedness of an adverse event will be determined by whether or not it is listed in the United Kingdom Summary of Product Characteristics (U.K. SmPC).

- **Associated With the Use of the Drug**

An adverse event is considered associated with the use of the drug if the attribution is possible, probable, or very likely by the definitions listed in Section 12.1.2.

## **12.1.2. Attribution Definitions**

- **Not related**

An adverse event which is not related to the use of the drug.

- **Doubtful**

An adverse event for which an alternative explanation is more likely, e.g., concomitant drug(s), concomitant disease(s), or the relationship in time suggests that a causal relationship is unlikely.

- **Possible**

An adverse event which might be due to the use of the drug. An alternative explanation, e.g., concomitant drug(s), concomitant disease(s), is inconclusive. The relationship in time is reasonable; therefore, the causal relationship cannot be excluded.

- **Probable**

An adverse event which might be due to the use of the drug. The relationship in time is suggestive (e.g., confirmed by dechallenge). An alternative explanation is less likely, e.g., concomitant drug(s), concomitant disease(s).

- **Very likely**

An adverse event which is listed as a possible adverse reaction and cannot be reasonably explained by an alternative explanation, e.g., concomitant drug(s), concomitant disease(s). The relationship in time is very suggestive (e.g., it is confirmed by dechallenge and rechallenge).

## **12.2. Procedures**

### **12.2.1. All Adverse Events**

All adverse events will be reported from the time a signed and dated informed consent form is obtained until completion of the last study-related procedure (LFU visit [telephone contact]) will be reported. Progression of the disease under study (hospitalized CAP) will not constitute an adverse event (lack of efficacy or insufficient clinical response should not be recorded as an adverse event). Those meeting the definition of serious adverse events must be reported using the Serious Adverse Event Form, including serious adverse events spontaneously reported to the investigator

within 30 days after the subject has completed the study (including poststudy follow up). The sponsor will evaluate any safety information that is spontaneously reported by an investigator beyond the time frame specified in the protocol.

All adverse events, regardless of seriousness, severity, or presumed relationship to study therapy, must be recorded using medical terminology in the source document and the CRF. Whenever possible, diagnoses should be given when signs and symptoms are due to a common etiology (e.g., cough, runny nose, sneezing, sore throat, and head congestion should be reported as “upper respiratory infection”). Investigators must record in the CRF their opinion concerning the relationship of the adverse event to study therapy. All measures required for adverse event management must be recorded in the source document and reported according to sponsor instructions.

The sponsor assumes responsibility for appropriate reporting of adverse events to the regulatory authorities. The sponsor will also report to the investigator all serious adverse events that are unlisted and associated with the use of the drug. The investigator (or sponsor where required) must report these events to the appropriate Independent Ethics Committee/Institutional Review Board (IEC/IRB) that approved the protocol unless otherwise required and documented by the IEC/IRB.

Subjects (or their designees, if appropriate) must be provided with a “study card” indicating the name of the investigational product, the study number, the investigator’s name, a 24-hour emergency contact number, and, if applicable, excluded concomitant medications.

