### EFFICACY EVALUATIONS/CRITERIA:

The primary endpoint, clinical cure rate, is defined as the ratio of the number of clinically cured subjects to the total number of subjects in the population, at the TOC visit.

The secondary endpoints consist of: microbiological eradication rate at the TOC visit, clinical cure rate in subjects requiring mechanical ventilation within 48 hours of enrollment, microbiological cure rate in subjects requiring mechanical ventilation within 48 hours of enrollment, clinical and microbiological relapse at LFU visit, and 30-day pneumonia-specific mortality rates (all deaths due to pneumonia within 30 days after randomization).

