### **12.2.2. Serious Adverse Events**

All serious adverse events occurring during clinical studies must be reported to the appropriate sponsor contact person by investigational staff within 24 hours of their knowledge of the event.

Information regarding serious adverse events will be transmitted to the sponsor using the Serious Adverse Event Form, which must be signed by a member of the investigational staff. The initial report of a serious adverse event may be made by facsimile (fax) or telephone. It is preferable that serious adverse events be reported via fax. After a telephone report of a

serious adverse event, a Serious Adverse Event Form must be completed by the investigational staff and transmitted to the sponsor within 1 working day.

All serious adverse events that have not resolved by the end of the study, or that have not resolved upon discontinuation of the subject's participation in the study, must be followed until any of the following occurs:

- the event resolves
- the event stabilizes
- the event returns to baseline, if a baseline value is available
- the event can be attributed to agents other than the study drug or to factors unrelated to study conduct
- when it becomes unlikely that any additional information can be obtained (subject or health care practitioner refusal to provide additional information, lost to follow-up after demonstration of due diligence with follow-up efforts)

The cause of death of a subject in a clinical study, whether or not the event is expected or associated with the investigational agent, is considered a serious adverse event. Any event requiring hospitalization (or prolongation of hospitalization) that occurs during the course of a subject's participation in a clinical study must be reported as a serious adverse event, except hospitalizations for:

- initial admission to the hospital for this episode of pneumonia
- social reasons in absence of an adverse event
- surgery or procedure planned before entry into the study (must be documented in the CRF)

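### Section 12.2.1 keeps all CAP progression out of adverse event reporting, while Section 12.2.2 makes a hospital stay prolonged by it a serious adverse event

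*Protocol*

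**What the plan says.** Section 12.2.1 (All Adverse Events) says "Progression of the disease under study (hospitalized CAP) will not constitute an adverse event" and adds in parentheses that "lack of efficacy or insufficient clinical response should not be recorded as an adverse event". Neither statement is limited to nonserious cases. The next sentence reads "Those meeting the definition of serious adverse events must be reported using the Serious Adverse Event Form".

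Section 12.2.2 (Serious Adverse Events) says the cause of a subject's death, "whether or not the event is expected or associated with the investigational agent, is considered a serious adverse event". It then covers hospitalization: "Any event requiring hospitalization (or prolongation of hospitalization) that occurs during the course" of a subject's participation must be reported as serious. Three exemptions follow: "initial admission to the hospital for this episode of pneumonia", stays for social reasons, and procedures planned before entry. Serious events must reach the sponsor within 24 hours of the site learning of them.

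Section 12.1.1 (Adverse Event Definitions and Classifications) counts aggravation of the baseline condition as an adverse event. It lists death, threat to life, and a new or prolonged hospital stay among the seriousness criteria.

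**The concern.** In a trial of hospitalized pneumonia, worsening of the pneumonia is a foreseeable reason for a longer stay. A site that follows 12.2.1 files nothing when this happens, because an event that is not an adverse event cannot be a serious one. A site that follows 12.2.2 files a serious adverse event form within a day. The two sites have seen the same event and both have followed the protocol.

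Section 11.4 tabulates adverse events by treatment group and gives particular attention to serious ones, and the IDMC monitors safety on an ongoing basis. The serious adverse event count would mix two definitions in proportions that nobody recorded. Expedited reporting would vary between sites in the same way.

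**Working it through.** The protocol states no figure that this point challenges, so the check sets the sections side by side for each type of event. All are current text.

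| Event | Section 12.2.1 | Section 12.2.2 | Result |
|---|---|---|---|
| Initial admission for CAP | Not addressed | Exempt | No conflict |
| Stay prolonged by worsening CAP | Not an adverse event | Serious adverse event, no exemption | Clear conflict |
| Readmission for CAP | Not an adverse event, if it counts as progression or lack of efficacy | Serious adverse event, no exemption | Arguable conflict |
| Death from pneumonia | No carve-out | Cause of death is explicitly serious | Wording clashes, but 12.2.2 is the specific rule |

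Three possible ways of resolving the conflict from the text:

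1. **Exemption list.** Naming the initial CAP admission as exempt implies that later CAP hospitalizations are reportable. This favors 12.2.2, but only by inference, and 12.2.1 still excludes progression outright.
2. **Definitions.** Section 12.1.1 would make worsening CAP an adverse event, since it aggravates the baseline condition, and a prolonged stay would make it serious. Section 12.2.1 then removes it. The definitions side with 12.2.2 but do not say that they override 12.2.1.
3. **The sentence after the exclusion.** "Those meeting the definition of serious adverse events must be reported using the Serious Adverse Event Form" could mean that serious progression is still reported. It could equally refer back to the adverse events in the section's opening sentence, from which progression has just been removed. Its antecedent is unclear, so it does not settle the matter.

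Readmission is only arguable because Section 9.3.1 defines relapse as the reappearance of signs and symptoms in a subject already rated cured at TOC. That is not obviously progression or insufficient response, although the same section then classes relapse as failure at LFU.

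Scale, by assumption only:

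- Section 11.1 assumes 90% cure in each arm. With 670 randomized 1:1, there are 670 / 2 = 335 per arm, and 335 × 0.10 = 33.5, or about 34 per arm (67 in total) not cured.
- The share of these whose CAP prolongs a stay is not given. In principle it runs from none to all. All is extreme, because failure under Section 9.3.1 also covers subjects who simply need additional antibiotics. Readmissions after cure at TOC would fall outside this pool.
- Section 1.2 cites 5% to 25% overall mortality in hospitalized CAP: 670 × 0.05 = 33.5 and 670 × 0.25 = 167.5, or about 34 to 168 deaths over both arms. These are background, all-cause figures. They concern deaths, where 12.2.2 is explicit, so they do not measure the conflict described here.

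**The case against.** The strongest defense is that keeping the efficacy outcome out of the adverse event tables avoids counting it twice, and that these events are recorded elsewhere. Pneumonia deaths more than 48 hours after the first infusion, and lack of efficacy requiring nonstudy antibiotics, are failures at TOC (Section 9.3.1). Relapse is assessed at LFU. Duration of hospital and ICU stay is collected for all subjects (Section 9.6). The IDMC reviews unblinded efficacy data as well as safety data (Section 3.1), so it would not be blind to an excess of treatment failures.

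Most of this stands. It limits the damage to safety reporting and does not remove the conflict. Resource-use data are summarized descriptively and are not expedited reports. A clinical outcome of failure does not show whether a stay was prolonged.

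A reader might infer more than the text supports:

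- **Pneumonia deaths are lost, or the mortality endpoint is compromised.** This does not follow. Section 12.2.2 deals with deaths explicitly, and the secondary endpoint, "30-day pneumonia-specific mortality rates (all deaths due to pneumonia within 30 days after randomization"), is defined independently of adverse event classification.
- **The comparison between arms is biased.** Investigators and subjects are blinded, so differing readings of the two sections should not vary systematically by arm. The expected effect is inconsistency and undercounting.
- **The serious adverse event rate would shift by a definite amount.** The protocol supplies neither the background rate nor the share of failures that would qualify.

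**Conclusion.** The contradiction is real and sits in a mandatory 24-hour reporting rule. It is clear for a hospital stay prolonged by worsening CAP and arguable for a readmission. For deaths, the specific rule in 12.2.2 governs in practice, although 12.2.1 should still be aligned with it. The consequence is that serious adverse event counts depend on which section a site follows.

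The size cannot be fixed from the protocol. The figure of about 34 subjects per arm rests on the planning assumption of 90% cure and shows only the rough size of the pool of treatment failures. It is not an estimate of affected events. Neither the primary noninferiority conclusion nor the 30-day mortality endpoint is threatened. The wording should be corrected because the fix is cheap and the rule is one that sites must apply the same way.

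**What to change.** Limit the exemption in 12.2.1 to nonserious events. Suggested wording: progression of CAP or lack of efficacy is not recorded as an adverse event unless it meets a seriousness criterion in Section 12.1.1, in which case it is reported as a serious adverse event under Section 12.2.2. Check 12.1.1 and 12.2.2 against the new sentence so that all three agree, and state whether relapse after cure at TOC is treated in the same way.

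A table of serious adverse events with and without CAP progression would help readers separate the two, but it is optional and can be left to the SAP.

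The cost is one amended sentence, somewhat more serious adverse event forms, and a slightly higher reported rate. The change concerns reporting only and does not alter treatment or assessments.

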### **12.2.2. Serious Adverse Events**

All serious adverse events occurring during clinical studies must be reported to the appropriate sponsor contact person by investigational staff within 24 hours of their knowledge of the event.

Information regarding serious adverse events will be transmitted to the sponsor using the Serious Adverse Event Form, which must be signed by a member of the investigational staff. The initial report of a serious adverse event may be made by facsimile (fax) or telephone. It is preferable that serious adverse events be reported via fax. After a telephone report of a

serious adverse event, a Serious Adverse Event Form must be completed by the investigational staff and transmitted to the sponsor within 1 working day.

All serious adverse events that have not resolved by the end of the study, or that have not resolved upon discontinuation of the subject's participation in the study, must be followed until any of the following occurs:

- the event resolves
- the event stabilizes
- the event returns to baseline, if a baseline value is available
- the event can be attributed to agents other than the study drug or to factors unrelated to study conduct
- when it becomes unlikely that any additional information can be obtained (subject or health care practitioner refusal to provide additional information, lost to follow-up after demonstration of due diligence with follow-up efforts)

The cause of death of a subject in a clinical study, whether or not the event is expected or associated with the investigational agent, is considered a serious adverse event. Any event requiring hospitalization (or prolongation of hospitalization) that occurs during the course of a subject's participation in a clinical study must be reported as a serious adverse event, except hospitalizations for:

- initial admission to the hospital for this episode of pneumonia
- social reasons in absence of an adverse event
- surgery or procedure planned before entry into the study (must be documented in the CRF)

### **12.2.3. Pregnancies**

Subject pregnancy must be reported by the investigational staff within 1 working day of their knowledge of the event using the pregnancy notification form. Any subject who becomes pregnant during the study must be promptly withdrawn from the study.

Follow-up information regarding the outcome of the pregnancy and any postnatal sequelae in the infant will be required.

## **12.3. Contacting Sponsor Regarding Safety**

The names of the individuals (and corresponding phone numbers) who should be contacted regarding safety issues or questions regarding the study

are listed on the Contact Information page(s), which will be provided as a separate document.

## **13. STUDY DRUG INFORMATION**

### **13.1. Physical Description of Study Drug(s)**

The study drugs consist of ceftobiprole medocartil 500 mg, ceftriaxone 2 g, linezolid 600 mg, and cefuroxime axetil 500 mg, and all will be provided by the sponsor.

Ceftobiprole is supplied in 10 mL vials containing 500 mg of lyophilized powdered. The powder is white to slightly yellowish or brownish in appearance.

Ceftriaxone is a white to yellowish-orange crystalline powder, which is readily soluble in water, sparingly soluble in methanol and very slightly soluble in ethanol.

Linezolid is supplied in single-use, ready-to-use infusion bags, as a sterile isotonic solution for i.v. infusion. Each mL contains 2 mg of linezolid. Inactive ingredients are sodium citrate, citric acid, and dextrose in an aqueous vehicle for i.v. administration.

Cefuroxime axetil is supplied as capsule-shaped, film-coated tablets.

### **13.2. Packaging**

Ceftobiprole will be supplied as vials of sterile lyophilized ceftobiprole medocartil containing 500 mg for i.v. administration.

Ceftriaxone will be supplied as vials containing 2 g of ceftriaxone sodium.

Study sites will provide placebo infusion solution.

The oral study drug (cefuroxime axetil) will be provided to the investigator sites in commercial packages labeled for use in this clinical trial.

Linezolid will be supplied in single-use, ready to use 300 mL infusion bags containing 600 mg linezolid.

### **13.3. Labeling**

Study drug labels will contain information to meet the applicable regulatory requirements.

